### Follow-up

Participants will be followed for 90 days. All clinical and HRQoL outcomes will be measured up to discharge and specifically at 30 and 90 days by face-to-face or telephone follow-up. CRP will be measured at 24 and 48 hours and every 24 hours during the hospital stay as per routine clinical practice. Clinical outcomes on follow-up include cumulative hospital and ICU stay including readmissions, predefined complications including organ failure, severe pancreatitis, infected pancreatic necrosis, surgical interventions, development of sepsis, pulmonary oedema or acute respiratory distress syndrome as well as mortality. Resource use data include medications, planned and unplanned tests and procedures and use of allied healthcare professionals (eg, physiotherapy, occupational therapy). HRQoL will be assessed using a validated questionnaire (EQ-5D).

### Sample size calculation

Formal sample size calculations are not appropriate for a feasibility study, hence a convenient sample size of 50 patients, randomised equally to the two groups, has been chosen. Sample sizes between 24 and 50 have been recommended to estimate the SD required for a sample size calculation for a subsequent large RCT aimed at evaluating the cost-effectiveness of GDFT.^23^

### Patient and public involvement

Patients involved in the trial preparation were surprised that there had been no progress in effective treatment for acute pancreatitis and felt that new therapeutic approaches were required. Some had experienced late complications and felt that better early treatment may prevent these late complications. The trial protocol was presented and discussed with patients to ensure that patient-centred outcomes such as survival and quality of life were appropriately measured, and advice was sought on the conduct of the study. The burden of the intervention was assessed by patient representatives and was thought to be ethical and appropriate. The outcomes of the study will be disseminated to the participants after review and formulation by our study patient representative. We wish to thank our patient representatives for their contribution and participation in this process.

### Trial management structure

A Trial Management Group (TMG) chaired by the chief investigator and comprising leads at different sites, ICU research nurses, the surgical team representative, research fellows, statistician, qualitative researchers and health economist will meet fortnightly to discuss trial progress and address issues in recruitment and delivering the intervention. Trial progress will be reported to independent data monitoring committee (DMC) comprising experts in acute pancreatitis, medical statistics and clinical trials every 6 months.

All serious complications and any mortalities will be immediately referred to the sponsor and reported to the TMG and independent DMC. The trial will be stopped in case of two or more treatment-related suspected unexpected serious adverse reactions.

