### Intervention

GDFT will be carried out for 48 hours. It can take up to 48 hours for the severity of pancreatitis to manifest and is considered the ‘golden’ period for interventions that may decrease severity.^21^ GDFT will be based on a standard algorithm which uses the SV derived from non-invasive cardiac output monitoring (NICOM) using the Cheetah NICOM (figure 2). The fluid administration regimen will be as follows: maintenance fluid should be administered at 1.5 mL/kg/hour (based on ideal body weight) using a balanced crystalloid solution to be ensured that a regulated volume of fluid was given per hour in order to avoid fluid overload in this group. Previous studies have been criticised for excessive maintenance fluid prescribed in the GDFT group.^22^ It was also felt that placing restrictions on the maintenance fluid prescription may influence decision-making in this group and affect the enthusiasm for clinicians to agree in patients participating in the study.

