**Figure 2 F2:**
[figure not shown]
Goal-directed fluid therapy (intervention) protocol. Flow diagram of SV optimisation with maintenance fluid administration. Patients randomised to goal-directed fluid therapy (GDFT) will receive a 1.5 mL/kg/hour of intravenous crystalloid maintenance fluid and four hourly visits from the trial nurses. At the first 4-hour visit, a bolus of 250 mL crystalloid over 5–10 min will be administered. An SV rise of >10% would indicate fluid responsiveness and a further cycle of fluid bolus is administered until there is no SV rise >10%. At the next four hourly visits if SV has dropped by >10% the cycle is repeated. SV, stroke volume.

On admission SV is recorded and an initial bolus of 250 mL of intravenous fluid (balanced electrolyte solution) is given over 5–10 min. If there is a sustained rise in SV of greater than 10% for 15 min or more, this indicates fluid responsiveness and a repeat 250 mL bolus will be given. If there is not a rise in SV of greater than 10% then the patient is deemed fluid unresponsive and no further fluid boluses are administered. SV monitoring continues four hourly and if it decreases by more than 10% a further fluid bolus is administered as above.

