Several secondary clinical, surgical, biochemical, safety and quality of life outcomes will also be collected. Mortality will be assessed as well. Clinical outcomes will include severity of pancreatitis as assessed by Glasgow score, proportion of patients with severe acute pancreatitis, necrotising pancreatitis, infected pancreatic necrosis, requiring ITU stay, requiring renal replacement therapy, requiring ventilation, requiring surgical interventions for complications related to pancreatitis and incidence of positive blood cultures. Resource use data for health economic analysis on length of hospital stay, length of ICU stay, and number of days ventilated, time to return to pre-pancreatitis activities, number of workdays lost (in those who work) and costs (NHS and personal social services perspectives) will be collected. HRQoL will be assessed using the well-validated EuroQol-5 Dimension (EQ-5D) questionnaire on admission as baseline and subsequently on days 7, 30 and 90. All complications of pancreatitis including treatment-related adverse events (postradiological and surgical complications as classified by Clavien-Dindo Classification) and serious adverse events related to intervention will be recorded up to discharge and at follow-up. Routine biochemical tests performed as part of clinical care including blood gases, liver function tests, clotting profile, renal function, amylase, full blood count and C-reactive protein (CRP) will be recorded on admission and daily up to 2 weeks and biweekly up to discharge. In addition, serum samples will be collected from participants in both groups on admission, 12, 24 and 48 hours’ time points and stored at −80° for future analysis of biomarkers in acute pancreatitis.

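### The only stopping rule in the protocol article counts unexpected reactions alone, so related serious overload-type events, which the protocol anticipates, would ordinarily not count towards it

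*Protocol article*

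**What the plan says.** Three parts of the protocol article bear on this point.

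- **Trial management structure** gives the rule: "The trial will be stopped in case of two or more treatment-related suspected unexpected serious adverse reactions". The sentence before it sets a reporting route that does not depend on expectedness: "All serious complications and any mortalities will be immediately referred to the sponsor and reported to the TMG and independent DMC". Scheduled reporting is separate: "Trial progress will be reported to independent data monitoring committee (DMC) comprising experts in acute pancreatitis, medical statistics and clinical trials every 6 months".
- **Intervention** explains why hourly maintenance fluid in the GDFT arm is fixed: so that "a regulated volume of fluid was given per hour in order to avoid fluid overload in this group".
- **Follow-up** lists predefined complications, among them "development of sepsis, pulmonary oedema or acute respiratory distress syndrome as well as mortality".

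Two other places touch on harm. Outcome measures says that "serious adverse events related to intervention will be recorded up to discharge and at follow-up", with no split into expected and unexpected. Progress to full trial, criterion (C), limits how far the 90-day complication rate under GDFT may exceed that of control, as a condition for going on to a definitive trial.

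**The concern.** Safety of the intervention is a secondary endpoint in the Abstract and an aim in Study design and setting. A stopping rule should therefore respond to the kinds of harm that the design already has in view. This one names a number, a consequence and a filter, and the filter is the weak part. Restricting the count to unexpected reactions makes the rule respond to surprises, while event types named in advance would ordinarily be screened out before counting.

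At stake is what happens during the trial if several GDFT patients have serious overload-type events judged related to the intervention. The stated rule could remain unmet, and the final report could truthfully say so, even though a pattern of related serious harm had occurred.

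**Working it through.** The rule has no stated error rate or power, so there is no figure of the plan's own to reproduce. The check is mainly a reading of the sections together, followed by an illustration of scale.

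**Step 1. What must be true for an event to count.** It must be suspected to be treatment-related, serious and unexpected. Two such events stop the trial.

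**Step 2. Which events the article names beforehand.** Intervention names fluid overload in the GDFT arm. Follow-up names pulmonary oedema and ARDS as predefined complications. The article gives no definition of unexpected and no list of expected reactions. Without one, an event type that the protocol itself names would ordinarily be classed as expected.

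**Step 3. Does another provision attach a consequence during the trial?**

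| Provision | Covers expected events? | Stated consequence during the trial |
|---|---|---|
| Stopping rule | No | Stop at two |
| Immediate reporting of serious complications and deaths | Yes | None stated beyond reporting |
| Recording of related serious adverse events | Yes | None; data collection |
| Adverse events reported by group in the analysis | Yes | None; reported descriptively |
| Progression criterion (C), 90-day complications | Yes | None; decides on a later trial |

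Only unexpected reactions carry a stated consequence while patients are being treated.

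**Step 4. Scale (illustration).** Inputs: n = 25 patients in the GDFT arm (Abstract, Methods and analysis), and a rate p of serious, treatment-related overload-type events. The article does not give p, so I assume a range of 2% to 30%. With independent patients,

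P(at least 2 events) = 1 − (1 − p)^25 − 25 · p · (1 − p)^24.

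For p = 0.10: 1 − 0.0718 − 0.1994 = 0.729.

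| Assumed p | P(at least 2 among 25) | Count under the current rule if classed as expected |
|---|---|---|
| 2% | 0.089 | 0 |
| 5% | 0.358 | 0 |
| 10% | 0.729 | 0 |
| 20% | 0.973 | 0 |
| 30% | 0.998 | 0 |

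The threshold of two is borrowed from the existing rule for illustration only. The middle column also shows how often a review trigger at that number would be reached.

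**The case against.** The strongest reply is that foreseen harm is not left unwatched. All serious complications and deaths go to the sponsor, the TMG and an independent DMC at once, whether expected or not, and the TMG meets fortnightly. **This stands.** A reader might infer from the six-monthly DMC schedule that serious events could build up unseen between reports. The text does not support that: the six-monthly reports concern trial progress, and serious events have their own immediate route. What is missing is a stated consequence, not notification.

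Two further stronger readings are tempting and should be resisted.

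- *That overload-type events could never trigger the rule.* This is not shown. Unexpected is undefined in the article, an outcome collected at follow-up is not the same as a listed expected reaction, and an event of a foreseen type can still be classed as unexpected, for instance because of its severity. The supportable wording is that such events would ordinarily not count.
- *That the protocol foresees this harm from the fluid boluses.* The phrase "in order to avoid fluid overload in this group" belongs to the explanation of maintenance fluid, and Follow-up lists pulmonary oedema and ARDS without attributing them to any part of the intervention. The point needs only that these events are named in advance.

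It can also be said that the full protocol or a DMC charter may hold an expectedness list, further criteria or a DMC power to recommend stopping. That is possible, and the absence of those details from an article is not the complaint. The complaint concerns a rule that the article does state, whose filter sits badly with what the article says elsewhere. Any fuller document would still need to be reconciled with it.

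**Conclusion.** The concern holds in limited form. The one stopping rule stated in the article is confined to unexpected reactions. Related serious events of types that the article names in advance would ordinarily fall outside it, and their immediate reporting carries no stated review or stopping consequence. Criterion (C) applies only after the trial, to the decision on progression.

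The size cannot be taken from the document. Over assumed event rates of 2% to 30%, the chance of at least two such events among 25 GDFT patients runs from 9% to over 99%, and none would count if classed as expected. This rests on independent patients, on the assumed rates, and on the ordinary practice of treating pre-named event types as expected. It is a weakness in safety oversight that should be corrected. It does not invalidate the trial, and it does not show that patients would go unmonitored.

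**What to change.** Reconcile the stopping rule in Trial management structure with the harms named in Intervention and Follow-up:

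1. Leave the existing stop for unexpected reactions exactly as it is. Replacing it with a review would loosen a safeguard already in place.
2. Add that treatment-related serious adverse reactions, anticipated or not and expressly including overload-type events (fluid overload, pulmonary oedema, ARDS) judged related, are counted as they are reported.
3. State that reaching a number set by the DMC prompts an unscheduled DMC review with a recommendation on whether to continue.
4. Say where expectedness is defined, or define it.

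The cost is a sentence or two in the protocol and the matching text in the DMC charter. Reporting is already immediate, so no new data flow is needed. The downside is possibly an extra DMC review; the DMC can weigh that when it chooses the number.

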### Data collection and analysis

Recruitment data which include number of eligible patients presenting to the emergency department, number of patients screened, number of patients consenting and number of patients randomised are recorded in a recruitment log in the emergency department. A Consolidated Standards of Reporting Trials diagram will be presented to provide a detailed description of participant numbers at each time point during the trial.^24^ A paper CRF is created for each participant enrolled into the study. The data collected on the paper CRF are then transferred to a secure online database using the Research Electronic Data Capture platform.

Since this is a feasibility study, all analyses other than recruitment rate and withdrawal rates should be considered exploratory. The two groups will be compared to ensure they have similar baseline characteristics (box 2) using means and SDs or medians and IQRs for continuous variables, as appropriate, and frequency counts and percentages for categorical variables.

Box 2Baseline characteristics of patientsThe intervention group and the control group should have the following baseline characteristics:Age.Sex.Ethnicity.Body mass index (BMI).Time since onset of symptoms.Presumed cause of pancreatitis.Comorbidities.Baseline observations.Baseline renal function.Baseline blood gas parameters.Glasgow severity score on admission.Intravenous fluids prior to intervention.

For the primary outcome, that is, feasibility, the proportion of patients who consent to be randomised and the rate of withdrawal from GDFT protocol will be presented with a 95% CI. The median number of complications, graded by the Clavien-Dindo Classification, in each group will be presented. The proportions of people with complications between the two groups will be presented and compared using appropriate statistical test and 95% CI.

For the secondary outcomes, among patients who participate in the trial, all clinical and surgical outcome measures will be presented for each group separately using the mean, SD, median, minimum and maximum for continuous outcomes and using frequencies and proportions for categorical variables.

Quality of life will also be summarised for each group using mean profile plots over time. The mean difference in quality of life scores between the two groups at 7 days up will be presented with a 95% CI.

Kaplan-Meier survival estimates and plots will be presented to compare survival rates between the two groups.

All other secondary outcomes collected over time will be summarised for each group using mean profile plots. Mean differences for continuous outcomes and difference in proportion for binary outcomes shall be presented, with appropriate 95% CIs, at 30 and 90 days.

The number and nature of adverse events shall be reported for each group. No formal comparisons between the groups will be made and no hypothesis tests will be carried out. The results will inform us how sensitive the outcome measures are and, along with other information, will be used to determine the primary outcome of a subsequent large RCT. The results will also inform a sample size calculation for the primary outcome chosen.

### Assessment of feasibility

This is a feasibility study and one aspect of this feasibility evaluation is the ability to recruit patients with acute pancreatitis into a trial of this nature. According to hospital episode statistics, an in-house review of admissions for acute pancreatitis to the Royal Free Hospital over the last 3 years showed 107 cases per year. After excluding patients who were transferred from another hospital for tertiary care, those who required immediate ICU admission, those with chronic pancreatitis in whom an acute exacerbation could not be confirmed by internal consensus criteria, current or past cardiac failure, or unable to provide fully informed consent, 80 patients per year would be eligible for this trial from a single centre. With a second centre we would anticipate 120 suitable patients per year. We anticipate recruiting at least 30% of potential participants which equates to 36 participants annually and a recruitment time of 17 months to recruit the 50 patients.

For feasibility assessment, a recruitment log will be used to collect information on suitability and consent rate as well as availability of trials team for GDFT, consent, failure to commence ward GDFT, withdrawal with reasons and failure to complete the study. In case of lower than anticipated recruitment at 6 months, we will perform the following: (A) analyse the results of the qualitative research earlier and identify the reasons for poor recruitment (and take actions to resolve the problems) if we get the anticipated number of patients screened but the recruitment rate is lower than anticipated; (B) recruitment of additional centres if we do not get the anticipated number of potential participants screened but the recruitment rate is at least as good as the anticipated rate; (C) a combination of the above if the number of potential participants screened and the recruitment rate are lower than anticipated.

We will explore the reasons for participation and non-participation of eligible patients, and patients and clinicians’ acceptability of the trial to assist in optimisation of recruitment strategies employed for the definitive trial. Non-participation can be related to how the clinical trial is presented to the patient, and how the patient assimilates this information. It is therefore important to understand how patients perceive information about potential participation and their experiences of receiving information relating to the trial. Interviews with a sample of eligible patients will explore patient perspectives of treatment, their understanding of the two treatments, reasons for taking part or refusing the trial and the acceptability of randomisation between the procedures. Interviews with clinical staff will explore their views about the trial, clinical equipoise and their understanding of the recruitment challenges. Semistructured interviews will be informed by a topic guide developed in conjunction with the TMG which includes patient representatives. Patient information sessions (recruiter meetings) will be audio recorded to examine how information is presented, and identify issues potentially affecting trial recruitment. Patient information sessions will be analysed at an early stage if there is poor recruitment and will inform the development of any additional training materials for recruitment for the definitive trial.

### Progress to full trial

The criteria to progress to a subsequent full trial will be determined quantitatively as (A) consent rate of at least 30%, the ability to recruit 50 patients to the study at the two sites over 17 months, (B) GDFT can be successfully performed within 6 hours of diagnosis of acute pancreatitis and can be continued until at least 48 hours after admission in a minimum of 80% of participants randomised to GDFT, and (C) the complication rate in the intervention group is not more than 10% higher than that of the control group at 90 days. A cut-off of 30% has been chosen for recruitment as this would be an achievable target in the definitive trial. A lower recruitment rate may indicate a lack of acceptability among clinicians and/or patients to participate in the definitive trial. In addition, a recruitment rate less than 30% is likely to make the subsequent definitive trial very expensive. A less than 30% recruitment may also highlight issues related to generalisability of the results, indicating a reduction in value of the subsequent definitive trial in terms of applicability in NHS.

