### Participants

Adults (>16 years) admitted as an emergency with acute pancreatitis will be included. Acute pancreatitis must be confirmed by the international consensus criteria (box 1).^19^ The exclusion criteria will be patients transferred for the management of complications of acute pancreatitis, requiring immediate admission to the ICU, chronic pancreatitis in whom an acute exacerbation cannot be confirmed, a history of cardiac failure in the past 3 months and those unable to provide fully informed consent.

Box 1International consensus criteria for acute pancreatitisAcute pancreatitis diagnosis confirmed with two of the following three features:Abdominal pain consistent with acute pancreatitis (acute onset of a persistent, severe, epigastric pain often radiating to the back).Serum amylase or lipase activity at least three times greater than the upper limit of normal.Characteristic findings of acute pancreatitis on contrast-enhanced CT (CECT) and less commonly MRI or transabdominal ultrasonography.

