### Outcome measures

The primary outcome of the trial will be an assessment of feasibility. In particular, the ability to identify and recruit patients at the selected sites to a study of acute pancreatitis. A recruitment rate of at least 30% over 17-month trial period will be deemed as successful. We will also assess the availability of study team for a condition presenting as an emergency, ability to randomise and commence ward GDFT within 6 hours of admission, completion rate of 48 hours of GDFT, rate of withdrawal (less than 20%) from GDFT protocol, reasons for withdrawal from GDFT protocol and proportion of complications in the two groups. Although the study is not powered to show differences in haemodynamic variables, we will analyse the haemodynamic data (such as SV and CO) at the end of the trial for patients in both groups to, at least, be able to conclude that we have optimised SV status of patients correctly according to the GDFT protocol drawn at the start of the trial. These data will be presented along with the main feasibility endpoints.

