## Trial status

The GAP trial opened for recruitment on 8 January 2018 for a period of 18 months.

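### The 30% threshold for the primary outcome and progression criterion A is attached to a consent rate in some places and a recruitment rate in others, and the two can differ

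*Protocol article*

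**What the plan says.** All references are to the protocol article. Its sections attach one threshold, 30%, to differently named quantities:

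- **Progress to full trial**, criterion A: "consent rate of at least 30%, the ability to recruit 50 patients to the study at the two sites over 17 months". The sentences that follow justify the 30% as a cut-off for recruitment, citing the cost and generalisability of the definitive trial if the recruitment rate is lower.
- **Outcome measures**: "A recruitment rate of at least 30% over 17-month trial period will be deemed as successful".
- **Assessment of feasibility**: "We anticipate recruiting at least 30% of potential participants which equates to 36 participants annually", from an anticipated 120 suitable patients a year at two centres.
- **Data collection and analysis**: recruitment and withdrawal rates are named as the only analyses that are not exploratory, but the quantity to be shown with a 95% CI next to the withdrawal rate is "the proportion of patients who consent to be randomised".

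The same analysis section has the recruitment log count eligible, screened, consenting and randomised patients separately. The feasibility section lists the consent rate and the availability of the trial team as separate items.

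A smaller mismatch lies behind the projected volume. The estimate of 80 eligible patients a year at one centre, and hence the 120, was made after removing patients with "current or past cardiac failure". The Participants section excludes "a history of cardiac failure in the past 3 months".

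**The concern.** This threshold defines success on the primary outcome and is the first rule for going on to a full trial, so one data set should give one answer. A consent rate and a recruitment rate agree only if every eligible patient is approached and every consenting patient is randomised.

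That is not assured here. The nurses must be contacted within 4 hours of diagnosis and treatment must start within 6, and the article names recruitment in the early hours of an unplanned admission as a major challenge. An eligible patient missed because no one was available, or because the window had closed, counts against a recruitment rate among eligible patients but disappears from a consent rate among those approached. The reasons given for 30% (cost, acceptability, applicability) concern the share of eligible patients who enter the trial. A consent rate among those approached does not measure that share.

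**Working it through.** **Inputs.** 120 suitable patients a year at two centres, 30%, 36 a year, 17 months and 50 patients (Assessment of feasibility); 50 patients in 17 months (criterion A). The article gives no number approached and no other pool size, so those below are assumptions.

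**1. Reproduce the plan's projection.**
- 120 × 0.30 = 36 a year, as stated.
- 50 / 36 × 12 = 16.7 months, rounded to 17, as stated.
- Eligible in 17 months: 120 × 17/12 = 170. Then 0.30 × 170 = 51, against the planned 50.

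The projection works with 30% as a share of all eligible patients. This is the nearest the article comes to a definition.

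**2. What the 50-patient target implies at the planned volume.** 50/170 = 29.4%. The second part of criterion A therefore holds recruitment close to 30% if the pool is as planned, however consent is counted.

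**3. When the two rates separate.** Fifty recruits fall below 30% of eligible patients once the pool exceeds 50/0.30 = 166.7. With assumed pools over 17 months:

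| Eligible pool | Relative to 170 | Per year | 50 / pool |
|---|---|---|---|
| 170 (plan) | 1.00 | 120 | 29.4% |
| 200 | 1.18 | 141 | 25.0% |
| 250 | 1.47 | 176 | 20.0% |

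**4. An example where the choice decides the result.** Assume 250 eligible, 150 approached, and 50 who consent and are randomised. Consent among those approached is 50/150 = 33.3% and 50 are recruited, so both parts of criterion A are met. Recruitment is 50/250 = 20.0% of eligible patients, which fails the Outcome measures threshold if that is read as the feasibility section derives it.

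**5. If consent is instead counted among all eligible patients,** it can exceed the recruitment rate only through patients who consent but are not randomised.

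**6. Precision of the proposed quantity.** At 51/170 = 30.0%, the exact (Clopper-Pearson) 95% CI is 23.2% to 37.5%.

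**The case against.** The strongest reply is that these are names for one quantity. Immediately after criterion A the article calls the 30% a recruitment cut-off. The analysis section pairs recruitment with withdrawal in one sentence and consent with withdrawal in another, which suggests that the first item is the same in both. The feasibility section supplies a denominator, and no section mentions a rate among patients approached. Loose wording may be the whole explanation. But the article itself counts eligible, consenting and randomised patients separately and lists consent apart from team availability, so the reader cannot safely treat the terms as equal. What stands is that the approached-only denominator is one possible reading and is not stated.

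Four stronger readings are tempting, and the article does not support them:

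- **That criterion A readily passes with recruitment well below 30%.** The requirement of "the ability to recruit 50 patients to the study at the two sites over 17 months" prevents this at the planned volume. A rate of 20% needs a pool 47% above plan as well as the approached-only denominator.
- **That 50 of 170 is itself a failure.** The one-patient gap (50 against 51) comes from rounding 16.7 months up to 17.
- **That the window is contradictory.** The Trial status note says that the trial "opened for recruitment on 8 January 2018 for a period of 18 months", but this describes how long recruitment was open. The outcome and progression sections both fix 17 months.
- **That missed patients are hidden.** Team availability, timely start and failure to commence are each assessed or logged, and a CONSORT diagram is promised. The information will exist; the question is whether the headline rate reflects it.

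An article may leave operational detail to a fuller document. Here, however, the stated sections give the primary threshold different names, which is more than omitted detail.

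**Conclusion.** The inconsistency holds. One threshold, used for both the primary outcome and the first progression rule, is attached to quantities that can differ, and the consent rate has no stated denominator. At the planned volume the consequence is small, because the 50-patient target keeps recruitment at 29.4% of 170. It becomes material only under two assumptions together: consent is counted among patients approached, and the eligible pool exceeds plan (25% at 200, 20% at 250).

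The cardiac-failure wording is a minor, separate matter. The volume estimate appears to exclude more patients than the enrolment criterion does, so the true pool could be larger than 120 a year, but the article gives no figure for the difference.

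Severity is moderate. The plan can be carried out as it stands and the necessary counts are collected, but the decision rule should not depend on which section is read.

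**What to change.** In Outcome measures, Data collection and analysis, and criterion A of Progress to full trial, use one quantity:

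- **Numerator:** patients randomised.
- **Denominator:** all patients in the recruitment log who meet the criteria in the Participants section, including those missed for time or staffing.
- **Window and precision:** the stated 17 months, with a 95% CI.

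Report consent among those approached separately, as a diagnostic of acceptability. Keep the 50-patient target as the second part of criterion A.

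As a minor point, reconcile the two cardiac-failure wordings and say which one the 80 and 120 a year rest on.

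The cost is wording only, since the log already records eligible, screened, consenting and randomised patients. The downside is that the headline rate may be lower than a consent rate would be.
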